## Abstract

**Background:**

The New South Wales (NSW) HIV Strategy 2016–2020 aims for the virtual elimination of HIV transmission in NSW, Australia, by 2020. Despite high and increasing levels of HIV testing and treatment since 2012, the annual number of HIV diagnoses in NSW has remained generally unchanged. Pre-exposure prophylaxis (PrEP) is highly effective in preventing HIV infection among gay and bisexual men (GBM) when taken appropriately. However, there have been no population-level studies that evaluate the impact of rapid PrEP scale-up in high-risk GBM. Expanded PrEP Implementation in Communities in NSW (EPIC-NSW) is a population-level evaluation of the rapid, targeted roll-out of PrEP to high-risk individuals.

**Methods:**

EPIC-NSW, is an open-label, single-arm, multi-centre prospective observational study of PrEP implementation and impact. Over 20 public and private clinics across urban and regional areas in NSW have participated in the rapid roll-out of PrEP, supported by strong community mobilization and PrEP promotion. The study began on 1 March 2016, aiming to enroll at least 3700 HIV negative people at high risk of HIV. This estimate took into consideration criteria for PrEP prescription in people at high risk for acquiring HIV as defined in the NSW PrEP guidelines. Study participants receive once daily co-formulated tenofovir disoproxil fumarate and emtricitabine (TDF/FTC) and are followed for up to 24 months. Follow-up includes: testing for HIV at 1 month, HIV and other sexually transmissible infections three-monthly, HCV annually and monitoring of renal function six-monthly. Optional online behavioural surveys are conducted quarterly. The co-primary endpoints are (i) HIV diagnoses and incidence in the cohort and (ii) HIV diagnoses in NSW.

**Discussion:**

EPIC-NSW is a population-based PrEP implementation trial which targets the entire estimated population of GBM at high risk for HIV infection in NSW. It will provide a unique opportunity to evaluate the population impact of PrEP on a concentrated HIV epidemic.

**Trial registration:**

https://clinicaltrials.gov/ (identifying number NCT02870790; registration date 14 August 2016), pre-results stage.

**Electronic supplementary material:**

The online version of this article (10.1186/s12889-017-5018-9) contains supplementary material, which is available to authorized users.

## Background

In New South Wales (NSW), Australia, research findings in HIV treatment as prevention [1] were followed in 2012 by a state-wide HIV strategy that had an over-arching aim of working towards the virtual elimination of HIV by 2020 [2]. In response to widespread implementation of policy actions directed towards HIV treatment as prevention [3], HIV testing rates and ART coverage among people diagnosed with HIV have increased considerably. By 2015, an estimated 93% of people with HIV in NSW were diagnosed; 89.3% of those diagnosed were on treatment, of which 91.3% had suppressed viral load over the preceding 12 months [4–6]. However, by the end of 2015, new HIV diagnoses in NSW had not declined substantially, and more than 80% of diagnoses continued to be in gay and bisexual men (GBM) [7]. Undiagnosed, and thus untreated, HIV infections among GBM [8], combined with increasing levels of condomless anal intercourse with casual partners [9], continued to drive the HIV epidemic despite very substantial increases in HIV testing and treatment. In order to achieve a significant reduction in new HIV diagnoses, additional strategies were required. In this context, the NSW HIV Strategy 2016–2020 proposed the population-level roll-out of HIV pre-exposure prophylaxis (PrEP), in combination with strengthening condom use, testing, and treatment, in order to move forward towards the ambitious goal of virtually eliminating HIV transmission by 2020 [10].

PrEP, in the form of combined tenofovir disoproxil fumarate 300 mg (TDF) and emtricitabine 200 mg (FTC), is effective for primary HIV prevention [11–13]. TDF/FTC has a favorable safety profile [14] and effectively penetrates the anorectal mucosa [15–17], which makes it an ideal prophylactic agent for GBM. PrEP efficacy is closely related to adherence [14], and adherence has been higher in people who are well-informed about HIV and PrEP [12, 13, 18]. TDF/FTC is now recommended as PrEP for people at high risk of HIV acquisition in national or regional guidelines in the US, Europe and Australia [19–21], as well as by the WHO guidelines globally [22].

At the time when EPIC-NSW began recruitment in March 2016, TDF/FTC as PrEP was not approved by the Australian Therapeutic Goods Administration (TGA) [23]. The first guidance for PrEP prescribing, which became available in NSW in October 2014 (formally published in 2016 [24]), defined the eligibility for PrEP in a PrEP demonstration project PRELUDE [25]. Funded by the NSW Government, PRELUDE provided access to PrEP to about 300 individuals, predominately GBM from November 2014–November 2016 [25]. However, PrEP demand rapidly surpassed the PRELUDE project’s capacity. Ongoing PrEP research in NSW [25–27], PrEP guidelines [24] and the new NSW HIV Strategy 2016–2020 [10] provided the framework for a population-level implementation project “Expanded PrEP Implementation in Communities in NSW”(EPIC-NSW).

While PrEP implementation among GBM has been in various stages of roll-out in other countries (e.g., in the US and France), EPIC-NSW is novel in being a hybrid research and implementation project targeting PrEP to all people at high risk of HIV infection in NSW, and measuring the public health benefit of this program with respect to reduction in HIV transmissions in the state.

This study protocol describes the population-level introduction of PrEP in NSW through a public health intervention, which is widely supported across the spectrum of researchers, clinicians, community organisations, and government policymakers.

## Methods / design

### Aim

EPIC-NSW aims to evaluate the population-level impact of the rapid roll-out of PrEP in individuals at high risk for HIV and to measure the impact on HIV incidence among GBM in NSW.

### Study design

EPIC-NSW is a prospective observational study of PrEP roll-out, implementation and impact. It is an open-label, single-arm, multi-centre trial, undertaken by a multidisciplinary team led by the Kirby Institute, UNSW Sydney. The target population is predominantly GBM at high risk of HIV acquisition through sexual contact. However, other high risk individuals who are eligible for PrEP under the NSW PrEP guidelines can also enrol in the study (see Table 1).

**Table 1 Tab1:**
[figure not shown]
Risk criteria for participation in the EPIC-NSW trial

Note: According to the EPIC-NSW protocol, only people classified at high risk for HIV acquisition based on the NSW guidance on PrEP can be enrolled into the study

All participants are advised to take daily TDF/FTC and attend study visits as per the schedule presented in Table 2. Follow-up includes testing for HIV at month one, for sexually transmitted infections (STIs) and HIV every 3 months, and for hepatitis C annually. Renal function tests are conducted at baseline, at 3months after enrolment, and every 6 months thereafter. Participants are also invited to join the optional study components: (i) self-administered online surveys of behaviour and medication adherence (at baseline and quarterly thereafter) and (ii) data linkage with the Australian Government and state agency health and disease-related registries approved by the NSW Population and Health Services Research Ethics Committee. The planned enrolment is a minimum of 3700 participants. Enrolment started on 1 March 2016. The project anticipates a total of 7400 person-years (PY) of follow-up on PrEP (up to 2 years of follow-up per person). To evaluate the uptake and impact of PrEP on the HIV epidemic in NSW, EPIC-NSW utilizes extraction of routinely collected data from electronic records maintained in clinical patient management systems across all sites using data extraction methods set up by the Australian Collaboration for Coordinated Enhanced Sentinel Surveillance (ACCESS study) [28].

**Table 2 Tab2:** EPIC-NSW study flowchart

Follow-up schedule	Screening/enrolment/baseline	Follow-up 1	Subsequent Follow-ups
Timeline	Week −2 or 0^a, b^	Month 1	Month 3 and every 3 months thereafter^c^
Informed consent	X		
Review eligibility	X	X	X
Medical history^d^	X		
Renal function (creatinine clearance)	X		X^e^
Serious adverse events, pregnancy (if applicable)		X	X
Hepatitis C testing	X		X^f^
STI testing ^g^	X		X
HIV testing^g^	X	X	X
Dispense study medication	X	X	X
Survey of adherence and behaviour	X		X^h^

^a^Results of all tests conducted in the preceding 2 weeks are accepted at enrolment. Only the HIV test should be conducted not earlier than 7 days within starting PrEP

^b^Visits may be combined if HIV test result available

^c^As per NSW and National PrEP guidelines

^d^Information in relation to eligibility for PrEP

^e^At 3 months and every 6 months thereafter

^f^Consider annual testing for HCV, or more often in men with substantial risk

^g^HIV and STI tests conducted per current standard of care according to the National HIV and STI testing guidelines. Data obtained electronically quarterly from ACCESS study

^h^Behavioural data collected on consenting participants

### Participants

We estimated the number of GBM at high risk of HIV acquisition using data available by the end of 2014. The number of males living in NSW who were aged 16–69 (n_1_ = 2,411,288) was derived from the Australian Bureau of Statistics [29]. According to the nationally representative Second Australian Study of Health and Relationships (ASHR2, 2013), 2.3% of 16 to 69 year-old male respondents in NSW self-identified as gay and 81.9% of these men had been sexually active in the last year [30] (n_2_ = n_1_*0.023*0.819 = 45,422 sexually active gay men in NSW). ASHR2 participants who identified as bisexual were not included in these estimates, because these men were considered much less likely to discuss their homosexual behaviour with clinicians and, ultimately, to be identified as candidates for PrEP assessment. After excluding HIV positive GBM (estimated n_3_ = 6550 [31]), the remaining men (n_4=_ n_2_- n_3=_38,872) represented sexually active men in NSW identifying as gay and at risk of acquiring HIV.

The database of the 2014 Sydney Gay Community Periodic Survey (SGCPS), an annual survey of behaviour among gay community engaged GBM in NSW [32], was used to determine the proportion of GBM at high risk of acquiring HIV who would be eligible for PrEP according to the NSW PrEP guidelines ([24]. Men were considered to be high risk if they reported at least one of the four high-risk behavioural eligibility criteria in the NSW PrEP guidelines. These were related to being a regular partner of an HIV-infected man without HIV viral load suppression, having receptive condomless anal intercourse (CLAI) with casual partners, reporting a recent anal STI diagnosis or syphilis, or methamphetamine use. (Table 1). The SGCPS indicator of having had within the preceding 6 months, ten or more casual partners was used as a proxy indicator for on-going sustained risk within the next 3 months. In total, 8.6% of HIV negative or HIV status unknown 16–69 year-old GBM reported at least one of these criteria. We assumed this proportion to be generalizable to all gay-identifying men in the population, and applied it to the number of sexually active gay-identifying men at risk for HIV in NSW to calculate the minimum number of men eligible for PrEP in NSW (N = n_4_*0.086 = 3343). We recognise that the inclusion in the estimate only of men reporting at least ten casual partners in the previous six-month period is a strict definition of those likely to have on-going risk, and that some men who have had fewer casual partners would also meet the criteria for PrEP eligibility in NSW. Allowing for loss to follow up, the study team considered that enrolling 3700 would represent a sufficiently high proportion of those truly at high risk of HIV infection at the time when PrEP use was not high (recent PrEP use was reported by just 4% of non-HIV-positive men in the 2016 SGCPS [9]). Additionally, it was considered that target enrolment of 3700 participants within existing sexual health services was feasible.

The previously conducted  Australian Health in Men Study found that each of the four high-risk factors were associated with an HIV incidence of above 1.8 per 100 person years [21]. Assuming a similar baseline HIV incidence in the EPIC-NSW cohort, a sample of 3700 participants, with 80% retention over the course of one year, will have 99.2% power to detect a 50% reduction in HIV incidence during the course of the first year on PrEP and 100% power to detect an 84% reduction in HIV incidence (as in European randomised trials of high-risk gay men on PrEP [12, 13]).

### Study medication

All participants receive sufficient supply of daily oral TDF/FTC for self-administration until the next scheduled follow-up visit. A 2000 person-year (PY) supply of TDF/FTC was provided by Gilead Sciences, Inc., and 5400 PY of generic TDF/FTC equivalent were purchased from Mylan Laboratories Ltd. The procurement process was competitive and occurred within a framework for ensuring safety and security of the supply chain, and the quality and bioequivalence of the generic TDF/FTC with Truvada®. Participants’ ongoing access to PrEP after study completion will be facilitated by clinicians at their last study visit.

### Study eligibility

Eligibility for this study is guided by the NSW Health guideline on Pre-Exposure Prophylaxis of HIV with Antiretroviral Medications. To be eligible, participants must be aged 18 years or over, live or visit NSW regularly enough to be able to attend clinics for follow-up assessments, be documented as HIV negative at enrolment or within 7 days of starting PrEP, and be at high and ongoing risk of acquiring HIV through sexual exposure as established by the behavioural risk criteria (see Table 1). Excluded from participation are individuals infected with HIV-1, or with symptoms consistent with acute HIV infection. If HIV status is indeterminate at the enrolment visit, the start of TDF/FTC is delayed for at least 1 month, to confirm HIV negative status. The full list of inclusion and exclusion criteria is presented in Table 3.

**Table 3 Tab3:** Inclusion and exclusion criteria for participation in the EPIC-NSW study

Inclusion criteria	Exclusion criteria
1. HIV negative at enrolment, with a negative HIV test result documented within 7 days of initiating PrEP	1. HIV-1 infected or has symptoms consistent with acute viral infection (If HIV positive status is not confirmed by testing, delay starting PrEP for at least 1 month and reconfirm negative HIV-1 status).
2. At high and ongoing risk for acquiring HIV infection through sexual exposure (as defined by Behavioural Eligibility criteria presented in Table 1)	2. Having an estimated creatinine clearance (glomerular filtration rate [GFR]) <60 ml/min
3. Aged 18 years or over	3. Having or developing clinical symptoms suggestive of lactic acidosis or pronounced hepatotoxicity (including nausea, vomiting, unusual or unexpected stomach discomfort, and weakness)
4. Live in NSW or visit NSW enough to attend clinics for follow-up assessments	4. Concurrently taking a nephrotoxic agent (e.g., high-dose non-steroidal anti-inflammatory drugs / NSAIDs)
5. Willing and able to provide informed consent	5. Allergic to TDF and/or FTC (based on self-report or recorded)
6. Medicare ineligible individuals may be enrolled if the clinical service is able to cover the costs of monitoring of the patient	6. Concurrently taking prescribed products containing FTC or TDF other drugs containing lamivudine
	7. Factors or conditions that may compromise a participant’s access to health services for follow-up (incarceration or planned relocation and potential absence from NSW for the duration of the study)

### Enrolment of participants

Over 20 clinical sites in urban and regional areas of NSW are participating in the project, including public HIV and sexual health services and private general practices with expertise in HIV antiretroviral medication prescribing (see participating health services in Appendix). Clinical sites are eligible to participate if they: (i) are willing to participate in PrEP roll-out; (ii) can enroll at least 10 patients at high risk for HIV who are eligible for PrEP; (iii) are able and willing to follow the study protocol, and (iv) are participating or willing to participate in the ACCESS study and have a patient management system which enables automated electronic transfer of the study variables, or alternatively are willing to complete manual data entry.

Study promotion materials (e.g., paper and electronic posters, flyers, cards and social media) were developed by NSW’s peak gay and lesbian health organisation, AIDS Council of New South Wales (ACON), in consultation with clinicians, researchers and the NSW Government. Their branding style is consistent with the highly recognisable ‘Ending HIV’ campaign from the NSW Ministry of Health communication framework [33]. Other promotion activities conducted by ACON include establishment and management of a list of people interested in PrEP prior to study initiation, online information about study enrolment, community forums and engagement with specific groups of GBM (e.g., GBM of Asian background). The NSW Sexual Health Infolink (SHIL), a NSW Health service, triages potential participants and conducts referral to participating clinics. The study is also promoted on social media and a variety of websites including the study website (https://epic-nswstudy.org.au), the NSW Health Ending HIV (http://www.health.nsw.gov.au/endinghiv) page, ACON’s website (https://www.acon.org.au/what-we-are-here-for/hiv-prevention) and the websites of some participating clinics. ACON in partnership with PozHet (community organisation of HIV positive heterosexual people) also developed promotional materials on PrEP for the heterosexual community.

Potential participants at high HIV risk are identified among patients attending clinical services based on information available to the clinics, including previously reported high risk behaviour, recent diagnosis of a rectal STI or syphilis, current use of PrEP obtained elsewhere (e.g., purchased online, prescribed in previous demonstration study PrELUDE) or post-exposure prophylaxis (PEP). Some patients are self-referred as a result of promotion or word of mouth, or referred to participating clinical services by other health service providers.

Upon presentation to health services, potential participants receive information about PrEP and the EPIC-NSW from clinicians or trained peer educators from ACON. In some clinics, trained peer educators provide information about PrEP individually or in group sessions. Risk assessment and eligibility screening for PrEP is conducted using a brief online questionnaire by clinicians. An initial assessment may also be done by a peer educator. In all participating sites, trained clinicians (doctors and nurses) conduct initial risk assessment, and two participating sites additionally use trained peer educators from ACON for onsite or outreach recruitment.

Patients willing to proceed with enrolment into EPIC-NSW are asked to provide individual written informed consent (see Additional file 1 for patient information and consent form) and then assessed for all remaining study inclusion and exclusion criteria described in Table 3. The study consent form also includes three separate optional consents to:(i)participate in a brief quarterly online survey about adherence and risk behaviour;(ii)link the person’s details to the HIV and STI Registries in NSW, and/or(iii)be contacted in the future for other research projects.

Participants are able to change or withdraw their consent to participate in any or all aspects of the study at any time during the course of the study.

To ensure that EPIC-NSW provides equitable access to PrEP to all eligible people in NSW, ACON identified the six most commonly used community languages for non-native English speakers in NSW (including Chinese, Thai, Spanish, Indonesian, Portuguese and Arabic). Consent forms and study promotional materials have been translated/back-translated into these six languages.

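### The cohort takes in people already on PrEP, but the power statement and the uptake endpoint treat every participant as a new starter

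*Protocol article*

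**What the plan says.** All references are to the protocol article.

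- **Recruitment.** Enrolment of participants lists, among the ways of identifying candidates, "current use of PrEP obtained elsewhere (e.g., purchased online, prescribed in previous demonstration study PrELUDE". The Background puts that demonstration project at about 300 people.
- **Baseline.** Participants reports that "each of the four high-risk factors were associated with an HIV incidence of above 1.8 per 100 person years" and continues: "Assuming a similar baseline HIV incidence in the EPIC-NSW cohort, a sample of 3700 participants, with 80% retention over the course of one year". The cohort "will have 99.2% power to detect a 50% reduction in HIV incidence during the course of the first year on PrEP", and has "100% power to detect an 84% reduction in HIV incidence".
- **Uptake.** Table 4 pairs the objective on PrEP uptake in high-risk men with the rate of enrolment, by clinic type and location.
- **Eligibility.** Table 3, exclusion 6, reads: "Concurrently taking prescribed products containing FTC or TDF other drugs containing lamivudine". Inclusion 1 and Study visits tie the negative HIV test to a 7-day window around the start of PrEP.
- **Analysis.** Data analyses computes cohort incidence as infections over person-years after prescription. Separately, it compares state surveillance data for the 12 months before recruitment with the 12 months after 3700 people are recruited.

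**The concern.** A person who arrives already on PrEP is not in a first year on PrEP, and is not moved by enrolment from an off-PrEP rate to an on-PrEP rate. The article's stated aim is the impact of the roll-out. If the cohort rate is set against 1.8 and the gap is read as that impact, protection that these people already had is counted as the study's achievement. The uptake endpoint has the same weakness, because enrolment does not distinguish a new user from one who changed supplier.

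The eligibility text adds to this. Read literally, exclusion 6 bars people on prescribed TDF or FTC, yet the recruitment text names people prescribed it in the demonstration project. The 7-day test window also has no clear meaning for someone who began PrEP months earlier. Sites could resolve either point differently.

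**Working it through.** **Step 1: reproduce the stated power.** The inputs are 3700 participants, 80% retention, one year, p0 = 0.018 and p1 = 0.009. Two-sided alpha of 0.05 is assumed, as none is stated.

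n = 3700 × 0.80 = 2960 PY.

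One-sample test against a fixed rate: power = Φ{[p0 − p1 − 1.96·√(p0(1−p0)/n)] / √(p1(1−p1)/n)} = Φ{(0.009 − 1.96 × 0.002444) / 0.001736} = Φ(2.43) = 99.24%.

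This matches 99.2%. Poisson variance gives 99.16% and an exact Poisson test 98.5%. An 84% reduction gives 100.0%. A two-sample comparison with 2960 per group gives 85.1% and does not match. The power statement therefore implies a comparison with a fixed external 1.8.

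**Step 2: range for f, the share already on PrEP.** The article does not give f, so it has to be bracketed.

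- All of about 300 demonstration participants enrol: 300/3700 = 8.1%.
- Upper bound: the article says that "recent PrEP use was reported by just 4% of non-HIV-positive men in the 2016 SGCPS". Applied to its 38,872 sexually active HIV-negative gay men, 0.04 × 38,872 = 1555, and 1555/3700 = 42%. This needs every such user to be high risk, to have started before the roll-out, and to enrol.

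**Step 3: cohort rate with no added study effect.** Assume prior users already have the 84% protection used in the power statement: rate = 1.8 × (1 − 0.84f).

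**Step 4: chance of a significant result below 1.8.** At 1.8, 2960 × 0.018 = 53.28 infections are expected. The largest count with exact Poisson lower-tail probability of at most 0.025 is 38. The chance is P(X ≤ 38) at the rate from step 3. The last column is the power for a further 50% reduction from that rate.

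| f | Rate per 100 PY | Expected infections | P(X ≤ 38) | Power, further 50% |
|---|---|---|---|---|
| 0 | 1.80 | 53.3 | 1.8% | 99.2% |
| 8.1% | 1.68 | 49.7 | 5.2% | 98.8% |
| 20% (illustrative) | 1.50 | 44.3 | 19% | 97.5% |
| 42% (upper bound) | 1.16 | 34.5 | 76% | 91.9% |

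If prior protection is 50% rather than 84%, f = 8.1% gives a rate of 1.73 and a chance of 3.4%; f = 20% gives 1.62 and 8.2%.

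**Step 5: attribution.** If everyone on study has 84% protection, 53.28 × 0.84 = 44.8 infections are averted relative to 1.8. Those newly averted through the study number 44.8 × (1 − f): 41.1 at f = 8.1% and 25.9 at f = 42%.

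**The case against.** The strongest reply is that no planned analysis makes the error. The figure of 1.8 appears only in the power statement, and the cohort endpoint is an incidence estimate with no stated test against it. The probabilities in step 4 therefore belong to a test inferred from the power statement. This stands, and it limits the point to how the cohort rate would be interpreted.

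A reader might infer several stronger things that the article does not support.

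- **That 1.8 is wrong for prior users.** It is an off-PrEP reference, and the article pairs it with an 84% reduction from randomised PrEP trials. For PrEP's own effect, what matters is the rate these people would have without PrEP, so 1.8 remains usable.
- **That the population co-primary endpoint is inflated.** Protection from PrEP taken in the 12 months before recruitment already lowers the pre-intervention count. If anything, it shrinks the before-after change.
- **That the power claim fails.** Even at the upper bound, power stays above 90%.
- **That nearly half the cohort could be prior users, from 4%/8.6% = 47%.** That ratio is a share of the estimated 3343 high-risk men. The cohort share is at most 42% of 3700, and it sets a 2016 survey figure against a population estimate from 2014 data.
- **That the article uses the 4% to dismiss prior use.** It uses the figure to argue that 3700 is a sufficient share of high-risk men.
- **That exclusion 6 flatly contradicts recruitment.** Its wording is garbled, it may be aimed at duplicate drug alongside study supply, and it does not clearly cover unprescribed online purchase. The conflict exists on a literal reading only.

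It can also be said that splitting naive from experienced participants is detail for an analysis plan. In part that is so: Study visits takes an antiretroviral history, and PrEP prescriptions are extracted from clinic records. But prescription records would miss online purchase, which the recruitment text names, and the listed contents of the enrolment database do not mention prior use.

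**Conclusion.** The point holds in a limited form. The article recruits continuing users, assumes an off-PrEP baseline and a first year on PrEP for everyone, and counts enrolment as uptake. As written, it overstates new uptake by however many participants only changed supplier. The cohort rate against 1.8 also cannot be read as the roll-out's added effect.

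The size depends on f, which is unknown. At the one documented count (about 300, if all transferred) the effect is small: 1.68 in place of 1.8, with a 5% chance of an apparent reduction. At the upper bound it is large: 1.16 and 76%. Both figures assume 84% prior protection, 2960 PY and two-sided alpha 0.05. The stated power and the before-after co-primary endpoint are not materially inflated. The eligibility passages need reconciling whatever the value of f.

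**What to change.** 1. Add an enrolment field for PrEP use before enrolment, including unprescribed purchase.
2. Keep the declared endpoints, but report cohort HIV incidence and enrolment separately for PrEP-naive and PrEP-experienced participants.
3. Base any statement about new uptake, or about the roll-out's added effect against 1.8, on the naive group.
4. Reconcile exclusion 6, and the 7-day test wording in Table 3 and Study visits, with the recruitment of current users under Enrolment of participants.

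The cost is one data field, stratified tables and a wording change. The downside is fewer person-years in the naive-only comparison.
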